The term “vitamin D” subsumes several structurally related pleiotropic secosteriod hormones, which are usually not further sub-classified [15]. Vitamin D plays a dual role as hormone and fat-soluble vitamin, regulating the expression of more than 900 genes [16, 17] via binding to the vitamin D receptor (VDR) a steroid hormone receptor [18]. Vitamin D plays a key role in calcium and phosphorus homeostasis [15], bone health [19] and various cellular and neuromuscular functions [15]. The vitamin D receptor and vitamin D metabolizing enzymes are expressed in the brain [20, 21]. Due to its pleiotropic function vitamin D is also involved in signaling cascades and neurobiological pathways [20], which may affect mental health. The active metabolite 1,25(OH)_2_D_3_ is thought to modulate the differentiation and maturation of dopaminergic neurons [22] and to affect brain serotonin concentrations [20, 23]. Low vitamin D status is associated with a range of adverse neuropsychiatric outcomes [24–32]. In particular, population based epidemiological and clinical studies showed an association of low 25(OH)-vitamin D serum levels (25(OH)D) with depressed mood [14, 26, 33]. Thus “sub-optimal 25(OH)D levels” may precipitate mental disorders [34, 35] and achievement/restoration of “optimal levels” may foster mental health and offer potentially a treatment option. However, the definition of the “optimal-level” of 25(OH)D, is still under discussion [36] since all currently pursued cut-offs are related to bone health outcomes [37] and based on suppression of PTH levels [38] with no evidence available with respect to an “optimal-level” for mental health [20]. The Institute of Medicine (IoM) defines 25(OH)D levels > 50 nmol/l (equals 20 ng/ml) as sufficient, whereas levels of 30–50 nmol/l or < 30 nmol/l are classified as at risk for inadequacy or as at risk for deficiency [37, 39]. In general many cofactors influence the vitamin D status [14, 40]. Apart from seasonal [41] and other environmental factors the risk of vitamin D insufficiency is also influenced by genetic factors. Two genome-wide association studies (GWAS) of 25-hydroxyvitamin D levels revealed genome wide associations for Single Nucleotide Polymorphisms (SNPs) at five gene loci (*GC*, *DHCR7/NADSYN1*, *CYP2R1*, *CYP2R2*, *CYP24A1*) [42, 43] and a more recent GWAS in a Punjabi Sikh population replicated three out of the five known loci and discovered a new one between *FOXA2* and *SSTR4* [44].

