## Methods

### Study design

The study is set up as a 28 days (based on the mean length of hospitalization of juveniles with depression), parallel group, double-blind, randomized, placebo-controlled trial to investigate the effect of an untreated vitamin D deficiency (placebo arm) on depressive symptoms in child and adolescent psychiatric patients.

We are currently enrolling 200 participants at one study site, the Department of Child and Adolescent Psychiatry, University Hospital Essen, University of Duisburg-Essen, Essen, Germany. In total, recruitment, intervention, and database lock are anticipated to be finalized within a two years period after First-Patient-First-Visit (FPFV).

Patients with a vitamin D deficiency, who meet the inclusion criteria (see below) and consented to the study will be randomized to receive either 2640 I.E. vitamin D q.d. based on recommendations for treatment of vitamin D deficiency in patients with chronic diseases (REF) or placebo on top of treatment-as-usual (TAU). Participants will be assessed psychometrically prior to study start and after 28 days with the self-rated Beck-Depression-Index –II [52] (BDI-II; selected instrument for inclusion criteria and primary endpoint) and additional psychological instruments (Table 1).

**Table 1 Tab1:** Scheduled measurements

Investigated item	Psychometric and sociometric questionaires/instruments	Executed /completed by	Time point(s)	Reference
Depression	BDI-II	Patient	Baseline, and end of study	[83]
Depression	DISYPS-II DES SBB	Patient	Baseline and end of study	[84]
Depression	DISYPS-II DES FBB	Parents	Baseline and end of study	[84]
Intelligence and mental development status	IQ,HAWIK, CFT, Son-R	Patient	Baseline	[85]
Structured Interview for clinical diagnosis	KIDDIE-SADS-PL	Clinical interviewer	Baseline	[66, 86]
Impulsivity	BIS	Patient	Baseline and end of study	[87]
Problem behaviors	CBCL	Parents	Baseline	[88, 89]
Problem behaviors	YSR	Patient	Baseline	[88]
Socioeconomic status	SES (KiGGS)	Parents	Baseline	[90]
Vitamin D status related questionnaire	SUN EXP QUEST	Patient	Baseline	[91, 92]
Habitual food and nutrient intake	FFQ	Patient	Baseline	[54]
Physical Activity	IPAQ	Patient	Baseline	[62]

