### Study procedure

The study is currently ongoing and scheduled for a duration of about two years and commenced with the “First-Patient-First-Visit” on June 15th 2016.

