#### Randomization and blinding

Children and adolescents meeting the above described eligibility criteria will be randomized as early as the third day, but at latest on the fifth day after admission for inpatient treatment. The study nurse under supervision of the principal investigator will transmit the following data to the Institute for Medical Biometry und Epidemiology (IMBE), Philipps-University Marburg, Marburg, Germany: pseudonymized patient code; BDI-II total score and 25(OH)D serum level. The IMBE will perform a block-wise randomization procedure and return a randomization code back to the study center which triggers the selection of the accordingly coded pill dispenser, which contains(blinded-mode) either vitamin D or identically looking placebo pills. The randomization is balanced for two BDI-II strata (total score values 14–23 and equal or greater than 24, respectively) and two 25(OH)D strata (25(OH)D < 12.5 nmol/l and 25(OH)D between 12.5–30 nmol/l). For 200 participants scheduled in total for randomization, the company Dr. B. Scheffler Nachf. GmbH & Co.KG (Bergisch Gladbach, Germany) has supplied 120 pill dispensers (100 for the protocol and 20 for losses/eventualities) with three times thirty vitamin D pills (dose strength: 880 I.E. per pill) and 120 dispensers with three times thirty identically looking placebos. These supplies will be sufficient for the planned 28 days of dosing with 2640 I.E. of vitamin D per day. The block-randomization code was generated prior to study start by the IMBE and sent to the company for an appropriate labeling of the pill dispensers.

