All applied psychometric instruments, sociometric questionnaires and outcome measures are displayed in Table 1. Depressive symptom severity is assessed as part of the screening by means of the BDI-II (self-rating) at the first visit to the clinic. At admission, clinical data including blood pressure and heart rate, use of medication and/or drugs (incl. Alcohol, smoking), puberty status according to Tanner [53], and auxiologic parameters (body height, body weight, and height and weight at birth) will be recorded. On the second day patients will meet with a therapist and the study nurse for a psychiatric interview and the completion of psychometric questionnaires. Patients will be asked to complete the BDI-II/ DISYPS-II -DES [52, 59] and the Barratt Impulsiveness Scale (BIS-11) [60]. Within the first week of hospitalization they will also be guided and asked to complete the CBCL (German version for school-aged children and adolescents of the Child Behavior Checklist [61]), Youth Self Report (YSR; German version [61] for patients and parents) and the International Physical Activity Questionnaire (IPAQ) [62]. The amount of sunlight exposure and outdoor activity will be assessed with a specialized questionnaire [63]. In order to study dietary habits and overall nutrition behavior as potential impact factors on mental health and co-variables for this study a Food Frequency Questionnaire FFQ [64] will be conducted.

Parents will be asked to answer questionnaires regarding their socioeconomic status (SES) [65].

The results of the initial clinical evaluation is then presented to a physician for children and adolescents psychiatry, who subsequently conducts a 30 to 60-min diagnostic evaluation according to DSM-IV criteria by means of the K-SADS-PL [66]. Within this session the medical history (psychiatric and somatic diagnoses) and previous treatment history will be obtained. Eligible patients will be randomized at the earliest and latest at day three and five after admission.

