#### Data analyses and statistical hypothesis

Analysis of the data will be conducted by a researcher blinded to the treatment condition. All statistical analyses will be performed after database-lock with “R” (www.r-project.org) at the Institute for Medical Biometry und Epidemiology (IMBE), Philipps-University Marburg, Marburg, Germany.

The main hypothesis of this study is, that treatment of depressive symptoms results in significantly lower improvement of BDI-II scores in the group of patients with vitamin D deficiency (placebo group) than in the supplementation group (verum group). The statistical hypothesis to be tested for the mean BDI-II score in the verum arm versus the placebo arm after 28 days of supplementation:

Null hypothesis: H_0_: BDI-II_verum_ = BDI-II_placebo_.

Alternative Hypothesis: H_1_: BDI-II_verum_ unequal BDI-II_placebo_.

A covariance analysis (ANCOVA) will be performed to contrast the outcome of the primary endpoint BDI-II in both intervention arms (two-sided level of significance; alpha = 0.05) in the Intention-To-Treat (ITT) population. The following co-variables will be considered: BDI-II at admission, 25(OH)D level at admission, age, and sex. Missing values will be considered via Last-Observation-Carried-Forward (LOCF) data, as far as available. Several sensitivity analyses will be conducted to prove for robustness, encompassing a per protocol analysis.

The secondary endpoint 25(OH)D and PTH levels will also be analyzed in the ITT population via an ANCOVA with the co-variables: 25(OH)D level at admission, age, and sex.

Further sensitivity analysis will be performed e.g. non-parametric analysis where patients with missing data will be set to lowest or highest ranks and repeated measure models will be applied. to hopefully confirm the results.

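### The 25(OH)D/PTH ANCOVA omits season, although the protocol names it as a factor in vitamin D status: a small, avoidable loss of precision, not bias

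*Protocol article*

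**What the plan says.** The section on data analyses and statistical hypothesis in the protocol article gives two covariate lists. For the primary endpoint: "The following co-variables will be considered: BDI-II at admission, 25(OH)D level at admission, age, and sex". For 25(OH)D and PTH, the analysis is "via an ANCOVA with the co-variables: 25(OH)D level at admission, age, and sex". Neither list contains season, date of admission or sun exposure. The sensitivity analyses named there (per protocol, extreme ranks for missing data, repeated measures) do not mention season either.

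The Background treats season as an established influence: "Apart from seasonal [41] and other environmental factors the risk of vitamin D insufficiency is also influenced by genetic factors". On timing, Study procedure says: "The study is currently ongoing and scheduled for a duration of about two years", with the first visit of the first patient on 15 June 2016. Study design is slightly tighter: "recruitment, intervention, and database lock are anticipated to be finalized within a two years period".

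Under Randomization and blinding, "The IMBE will perform a block-wise randomization procedure" and "The randomization is balanced for two BDI-II strata", together with two 25(OH)D strata. Calendar time is not a stratum. Under Data collection and outcome measures, "The amount of sunlight exposure and outdoor activity will be assessed with a specialized questionnaire", but no stated analysis uses that measurement.

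**The concern.** A study window of about two years lets admissions fall in every season. The outcome in question is measured only 28 days after baseline, and it moves with the calendar. Two patients who both enter at 25 nmol/l, one in spring and one in autumn, have the same covariate value in the planned model. Their expected day-28 values differ, because one is on the rising and the other on the falling part of the annual cycle. Baseline 25(OH)D cannot tell them apart, but the date can.

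What is at stake is the width of the confidence interval for the 25(OH)D difference and, more weakly, for PTH and the BDI-II. There is also a question of interpretation. The hypothesis contrasts corrected with uncorrected deficiency, so a reader of a null BDI-II result will want to know whether placebo patients stayed deficient in the sunny months.

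**Working it through.** **The plan's own figure.** The inputs from the Sample size section are a difference of 4 BDI-II points, SD 9, two-sided alpha 0.05, power 80% and attrition 20%.
- Normal approximation: n = 2 × (1.96 + 0.84)² × 9² / 4² = 79.5, so 80 per arm. The t-test gives 80.44, so 81 per arm, as stated.
- Attrition: 80 / 0.8 = 100 and 81 / 0.8 = 101.25, so the stated 100 per arm agrees within rounding.
- The calculation does not rely on any covariate. About 80 completers per arm, 160 in all, is used below.

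**Seasonal drift in 25(OH)D (inputs assumed).** Take an annual cycle 25(OH)D(t) = A sin(2πt/365), with A = 5 or 10 nmol/l, entry dates spread evenly over the year, and a residual SD s of 8, 15 or 20 nmol/l apart from the drift. The documents give none of these.
- Largest 28-day change = 2A sin(28π/365) = 2A × 0.2387, which is 2.4 nmol/l for A = 5 and 4.8 nmol/l for A = 10.
- SD of the drift over entry dates = largest change / √2, which is 1.7 and 3.4 nmol/l.
- Share of residual variance = drift variance / (drift variance + s²). The drift variances are 1.69² = 2.85 and 3.38² = 11.4.

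| A | s = 8 | s = 15 | s = 20 |
|---|---|---|---|
| 5 | 2.85/66.85 = 4.3% | 2.85/227.85 = 1.3% | 2.85/402.85 = 0.7% |
| 10 | 11.4/75.4 = 15.1% | 11.4/236.4 = 4.8% | 11.4/411.4 = 2.8% |

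The range is therefore roughly 1 to 15%. At its upper end (A = 10, s = 8, 80 per arm), the standard error of the difference is √75.4 × √(2/80) = 1.37 nmol/l without season and 8 × √(2/80) = 1.26 nmol/l with it. At A = 10, s = 15 the standard errors are 2.43 and 2.37.

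**BDI-II (share explained by season assumed).** Residual SD = 9√(1 − R²), with t-test power at 80 per arm.
- R² = 0: SD 9.00, power 79.8%
- R² = 0.01: SD 8.95, power 80.2%
- R² = 0.02: SD 8.91, power 80.6%
- R² = 0.05: SD 8.77, power 81.8%

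**Bias check.** A simulation of 3000 trials used 160 patients, four strata, blocks of 4 (assumed), season explaining 5% of outcome variance and no true effect. The mean estimated difference was −0.02 points both without and with season. Type I error was 4.4% without and 5.0% with season, with a Monte Carlo error of about 0.4 percentage points. Omitting season does not bias the comparison or inflate its error rate.

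**The case against.** The strongest reply is that this is a preference about covariates and not a defect. Leaving a prognostic variable out of a randomised ANCOVA is valid, and a Background sentence about season does not commit the analysis to adjusting for it. That stands. A reader might infer that the two-year window biases the 25(OH)D or BDI-II comparison. The documents do not support this, because allocation is randomised in blocks and the simulation shows no bias.

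The second reply is that the 25(OH)D contrast is probably well powered anyway. At residual SDs of 12 to 20 nmol/l and 80 per arm the standard error is 1.9 to 3.2, so differences of about 2.8 × 1.9 = 5 to 2.8 × 3.2 = 9 nmol/l already have 80% power. Entry is below 30 nmol/l and the Background puts sufficiency above 50, so correcting the deficiency should produce a larger difference. This also stands: no conclusion is shown to hinge on the adjustment.

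The third reply is that the size rests on free assumptions. It does. Amplitudes of 15 to 20 nmol/l would raise the share to as much as 42% (A = 20, s = 8), but they fit this sample poorly. A fall of 9.5 nmol/l would take a patient at 12.5, the upper limit of the lower stratum, to 3. Even 5 to 10 nmol/l applies one curve to every patient, including inpatients and those receiving vitamin D.

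Finally, an SAP that is not shown may add season, and the article introduces its further sensitivity analyses only as examples. If the SAP does so, nothing remains to be done. But the article states its covariate lists, so the point addresses a stated choice and not an omitted detail.

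**Conclusion.** The point holds as a minor improvement in precision, mainly for the secondary 25(OH)D endpoint. Season is absent from both stated covariate lists, and baseline 25(OH)D does not carry the direction of change over 28 days. The illustrative size is about 1 to 15% of the 25(OH)D residual variance, given annual amplitudes of 5 to 10 nmol/l, residual SDs of 8 to 20 nmol/l and even enrolment over the year. For the BDI-II it is at most about 2 power points if season explains up to 5% of the variance. No figure can be given for PTH. The primary analysis remains valid and the sample size is unaffected.

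Three stronger readings are tempting but lack support:
- That 25(OH)D is the trial's only check on the intervention: PTH is also analysed.
- That drop-out makes seasonal imbalance between arms likelier: nothing in the documents shows this.
- That sun exposure is recorded because of season: the protocol says only that the questionnaire explores factors influencing vitamin D status.

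**What to change.** Before database lock, pre-specify season of randomisation as a covariate in the 25(OH)D/PTH ANCOVA, either as the sine and cosine of the randomisation date (2 df) or as a summer versus winter half-year indicator (1 df). Include the same term in the BDI-II ANCOVA, or name that model as a sensitivity analysis so that the stated primary model stays as it is. Report day-28 25(OH)D by arm and half-year, so that readers can see whether placebo patients remained deficient in the sunny months.

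The cost is 1 to 2 degrees of freedom out of about 160 and one additional descriptive table. No measurement beyond the randomisation date is needed.

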## Discussion

Depressive disorders in childhood and adolescents are devastating and may affect the whole lifespan [73]. Treatment options for this age group are scarce [74, 75] and show only low to medium effect sizes [76, 77]. The drug development pipeline for psychiatric disorders is rather dry and no breakthroughs – especially not for the young population – can be expected in due time [78]. Driven by the medical need and the search for benign, complementary options, lifestyle management strategies including physical activity, healthier diets [13, 11] and strategies for vitamin supplementation [79] appear on the scene and should be scientifically and clinically investigated according to best practices [79].

Based on findings from observational studies one promising option to improve depressive symptoms is a supplementation with vitamin D. However RCTs in young psychiatric patients have not been performed [14]. Several of the reported RCTs in adult depression revealed methodological issues and biological flaws as brought to attention by Spedding [80], who found positive results only in cases of baseline 25(OH)D levels below current cut-offs and clinically diagnosed mental disorders: In studies without biological flaws, a statistically significant improvement in depression with vitamin D supplements [SMD = 0.78; 95 CI (0.24, 1.27)] was found, whereas in studies with biological flaws a worsening in depressive symptoms [SMD = − 1.1; 95 CI (− 0.7, − 1.5)] was found (*p* values were not reported). Surprisingly, many studies neither considered a pronounced vitamin D deficiency nor a clearly defined disease status, which might have led to biased conclusions. Thus RCTs focusing on effects of vitamin D in well defined, homogenous groups [45–47] of children and adolescencets with mental disorders are of substantial importance to clarify the importance of the vitamin D status on mental health.

The current study aims to increment the evidence base. Since this study was set-up to prove the effect of untreated vitamin D deficiency within a clinical setting with potentially limited hospitalization time, the intervention duration of 28 days is seen as a potential limitation and risk for the study outcome. However, in case of success this clinical setting might have an even higher impact on treatment strategies for the sake of children and adolescents with depressive disorders.
